##### Secondary outcomes

Secondary outcomes measured at each time point (baseline, 2, 4, and 8 weeks) will include self-reported sedentary behavior, back posture and mobility, and behavior-related variables with respect to the lower back.

We measure *sedentary behavior* through self-report using three items adapted from the International Physical Activity Questionnaire (IPAQ) [30]. To measure leisure-time sedentary behavior, the item stem “During the past 7 days, how much time did you usually spend sitting…” is followed by (a) “…on a typical weekday during leisure-time (e.g., after work, transport time home)?”, and (b) “…on a typical weekend day during leisure-time?”. For work-time sedentary behavior, the item stem is followed by “…on a typical workday?”. All three elements of sedentary time are answered by open-ended responses to hours and minutes spent sitting.

To assess activity at the micro level of the back, we developed a self-report questionnaire to assess *perceived back posture*,* back mobility*,* and back movement* during work and leisure-time: the Back Posture, Movement and Mobility (B-PMM) self-report questionnaire. The B-PMM self-report questionnaire consists of 13 items, 7 items measuring perceived back posture (e.g., “My back posture is very good.”), 5 items measuring perceived back movement (e.g., “I regularly change my back posture at work [e.g., leaning backwards in my office chair, rotating my shoulders, standing up].”) and 1 item assessing back mobility (“I am very flexible in the back.”). The items can be answered on a 6-point Likert scale (*1 = not true at all* to *6 = extremely true*). For a full German and English item list see Additional file 1. For posture and movement, a mean score of the corresponding items will be calculated. The validity of the B-PMM will also be tested by determining the agreement with the objective back measurement data from the present study.

*Back posture and mobility* are measured objectively once at baseline using the IDIAG M360^®^ MediMouse. This device is a hand-held computer-assisted electro-mechanical tool that allows the non-invasive and radiation-free assessment of the spinal shape using two rolling wheels that transfer the spinal contour via Bluetooth to a computer. For this, the tool is guided along the spine on the spinous processes starting at the C7 and ending at the caudal reference point or the top of the anal crease, respectively [32, 33]. The IDIAG M360^®^ MediMouse takes scans in the sagittal and frontal planes of the lumbar and thoracic spine (Fig. 3). After disinfecting the back, the spinous process of the C7 vertebrae is identified by manual palpation. The anatomical landmarks C7 and S3 act as the start and end points of the measurement. In total, participants will be measured in 12 different conditions (six in standing and six in sitting), which will take approximately 20 minutes. The validity and reliability were established in previous studies [33, 34]. The mobee ^®^ spine software (SportMed A.G. SA, Echternach, Luxembourg, version 4.5.0) will be used to process the raw data from the back posture and mobility measurements. For each of the 12 measurement conditions, the lordosis-, kyphosis-, and sacral angles as well as the angles at each spinal segment will be analyzed descriptively for each participant (*M* ± *SD*). In addition, the degree of deviation of the angles from the cohort mean (°), will be analyzed descriptively for each participant. The degree of deviation, which is the difference from the mean, will be defined < 1 *SD*, > 1 *SD* and *> 2 SD* from the mean of the cohort. A ‘back deviation-sum score’ for deviations > 2 SD will be calculated for posture and mobility. The score will range from 0 to 48 for posture (based on 12 test conditions at 4 different angles) and 0–32 for mobility (based on 8 test conditions at 4 different angles). All angles will be normalized to the mean value of the study cohort, which serve as physiological reference value for back posture and mobility. Both absolute scores and difference scores exceeding 2 standard deviations per measurement condition will be utilized as independent variables for multivariate analyses, and sum scores will be examined.

**Fig. 3 Fig3:**
[figure not shown]
Back posture and mobility measurements using the IDIAG M360^®^ MediMouse

We use multiple indicators to assess behavior-related outcomes with respect to the lower back (Table 1). *Subjective health with regard to the lower back* of participants will be assessed with a single item adapted from the Veterans Rand 12-Item Health Survey (VR-12) [35–37]. We ask participants to rate the question “How would you rate the health of your lower back?” using a Likert scale from 1 (*poor*) to 5 (*excellent*). In line with the time frame of the IPAQ, we instruct participants to think about the past 7 days when answering the item. *General health-related quality of life* (HrQoL) is measured with a modified Veterans Rand 12-Item Health Survey (VR-12) [35–37]. The modifications relate to the time frame and the inverted display of the response options for subjective health. These are displayed from 1 (*poor*) to 5 (*excellent*). In addition, we use the Patient Health Questionnaire (PHQ-4) [38] to screen participants for symptoms of *depression and anxiety*.

We use the Chronic Pain Grade Questionnaire (CPGQ) [39] to assess potential *low back pain intensity and disability*. We specifically instruct participants to think about their lower back when answering the items. Adjustments for pain location have been made before for back pain [40]. For the CPGQ, for exploratory purposes, we added an item specifically tailored to our research question: “In the past 7 days, to what extent has your back pain interfered with your leisure-time physical activity?”. To assess potential *disability due to back pain* we use the Roland-Morris Disability Questionnaire (RMDQ) [41].

##### Determinants of behavior-related and behavioral outcomes

Theory-derived psychological constructs will include self-report measures specific for LTPA, including *risk perception* [42], *outcome expectancies* [42, 43], *intentions*,* self-efficacy*,* action control* [43, 44], *social support* [45–47], *action and coping planning* [48]. *Habit strength* for LTPA will be measured with the Self-Report Behavioral Automaticity Index [49, 50]. Based on the fear avoidance model [15], we will also assess beliefs about the lower back, *fear of movement* using the German version of the Tampa Scale for Kinesiophobia [51, 52] and *pain catastrophizing* using the Pain Catastrophizing Scale [53, 54]. Theory-based job resources will include *job control* (Instrument for Stress-Oriented Task Analysis) [55], *recovery experience* (Recovery Experience Questionnaire) [56], and *organizational health climate* towards physical activity (Organisational Health Behavior Climate Scale) [57]. Time pressure will be assessed with the Instrument for Stress-Oriented Task Analysis [55]. To assess *positive and negative affect*, we use an adapted 10-item short version [58, 59] of the Positive And Negative Affect Schedule (PANAS) [60, 61]. The original item “distressed” was changed to “irritable”, and we added the two negative affect items “sad” and “stressed” (Table 2). *Self-regulatory capacity* is measured with the Brief State Self-Control Capacity Scale [62]. A detailed list of measurements is available on request from the authors.

**Table 2 Tab2:** Ecological momentary assessment questions asked daily during the intensive-longitudinal study period

Item	Domain	Morning	Afternoon	Evening
**Behavior**				
Have you been physically active during your leisure-time today? *1 (yes) – 2 (no)*; When did you start (time, e.g., 06:30 pm)? *Open answer format (hh: mm)*; What was the activity? *Open answer format*; How long did the activity last? (in min, e.g., 20 min) *Open answer format (min)*	Leisure-time physical activity	-	-	x
Have you carried out your plans from this morning? *1 (not at all true) – 6 (absolutely true)*,* 7 (I did not make any specific plans this morning)*	Plan enactment	-	-	x
Being physically active in my planned situation is something I do automatically. *[Hidden if plan enactment = 7] 1 (not at all true) – 6 (absolutely true)*	Habit strength	-	-	x
**Behavior-related outcomes with respect to the lower back**				
How is your lower back today? *1 (poor) – 5 (excellent)*	Subjective health in relation to lower back	-	-	x
How would you rate your low back pain as it is today? *0 (no pain) – 10 (worst pain imaginable)*; To what extent has your low back pain today interfered with your leisure-time physical activities? *0 (no interference) – 10 (I was unable to carry out any activities)*	Low back pain	-	-	x
**Activity-related variables**				
Today I intend to be physically active in my leisure-time. *1 (not at all true) – 6 (absolutely true)*	Intention	x	-	-
I am confident that today I can manage to be physically active in my leisure-time, even if it is difficult. *1 (not at all true) – 6 (absolutely true)*	Self-efficacy	x	-	-
Today, I received support from my colleagues or supervisor (Item 1)/friends or family (Item 2) with regard to my leisure-time physical activity. *1 (not at all true) – 6 (absolutely true)*	Social support	-	x	-
For today, I have already made a detailed plan on which occasions I can be physically active during my leisure-time. *1 (not at all true) – 6 (absolutely true)*; *[If ≥ 2 (not true)]* What activity(ies) are you planning to do? *Open answer format*; On which occasions (6 pm; in front of the television)? *Open answer format*	Action planning	x	-	-
**Job demands and resources**				
Did you work today? *1 (yes) − 2 (no); [If 1 (yes)]* From when until when did you work today? *From (time*, e.g.,* 9:00 am) ___ Until (time*, e.g.,* 4:00 pm) ___;* Have you taken at least one break of at least 15 min today? *1 (yes) − 2 (no)*; *[If 1 (yes)]* How long was your break? If you took more than one break, think of the longest. *From (time*, e.g.,* 12:00 pm) ___* *Until (time*, e.g.,* 1:00 pm) ___*	Working hours and breaks	-	-	x
Are you still working? *1 (yes) − 2 (no) – 0 (I did not work today)*; *[only for 1 (yes) and 2 (no)]* Are you working from home today? *1 (yes) − 2 (no)*	Work place	-	x	-
How often have you been under time pressure for professional reasons today? *1 (very seldom/never) – 5 (very often/always)*	Time pressure	-	x	-
Were you able to choose the way you did your work today? *1 (very seldom/never) – 5 (very often/always)*	Job control	-	x	-
This evening I didn’t think about my work at all. (Item 1)/ This evening I used the time to relax. (Item 2)/ This evening I did things that challenged me. (Item 3)/ This evening I felt I could decide for myself what to do. (Item 4) *1 (does not apply at all) − 5 (applies completely)*	Recovery experience	-	-	x

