#### Within-person research questions

At the within-person level, we hypothesize that higher-than-usual levels of LTPA are positively linked with low back health. We will examine these associations concurrently (same-day, t) and prospectively (from previous-day, t-1 to next day, t). We also expect individuals to engage in more LTPA than usual on days when their positive affect is higher and their negative affect is lower than usual. On days when individuals experience higher levels of job demands and lower levels of job resources than usual, we expect people to engage in lower levels of LTPA than usual. We will examine these associations concurrently (same-day, t) and prospectively (from previous-day, t-1 to next day, t). We will also describe day-to-day fluctuations in activity-related intention, low back pain, social support, planning, self-efficacy, and plan enactment.

In an additional, observational *N*-of-1 time-series approach including data-prompted interviews, we will examine whether these within-person predictors also hold relevance for a single individual. Qualitatively, we aim to understand the related mindsets, and the struggles, and resources involved in carrying out LTPA. This study expands on previous research by examining not only personal predictors but also the impact of social and work environments on low back health. Furthermore, we investigate strategies individuals use to maintain low back health.

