## Methods

### Study design and procedures

This study is a prospective longitudinal observational cohort study, taking place over a period of 2 months, with an intensive-longitudinal ecological momentary assessment (EMA) phase (Fig. 2). Participants provide self-report questionnaire data at baseline (Time 0, T0), with subsequent follow-up questionnaires (Time 1–3, long-longitudinal design; LL) collected electronically via an online survey platform (Unipark, Tivian XI GmbH, Cologne, Germany) from a study tablet or computer on-site (T0) or on a personal device at home (e.g., computer, tablet, smartphone; Time 1–3). The study will involve a 1.5 h baseline session at MSB Medical School Berlin or Charité Universitätsmedizin Berlin or participants’ workplace, during which demographics, PA and sedentary behavior, physical and mental health, as well as theory-driven psychological variables will be assessed. During the baseline session, participants will also undergo objective measurements of their back posture and mobility. Participants will then receive training in the time-sampling protocol, the handling of their Android study phone (Nokia 6.3) with the movisensXS app (movisens GmbH) and accelerometer (Move4, movisens GmbH). Starting at T0, participants will wear an accelerometer and will be asked to complete three daily questionnaires on their study smartphone for the following 14 days (intensive-longitudinal design; IL; Fig. 2). Participants will receive three alarm-triggered daily life surveys via the movisensXS app at 8 am (“morning questionnaire”), 3 pm (“after work questionnaire”), and 9 pm (“evening questionnaire”). Participants can delay responding until 3 h after the time prompt, and reminders are sent every 20 min during this window. After this time, the questionnaires will no longer be available to prevent backfilling. Daily life assessments take 2 to 6 min each to complete, resulting in a total of 1.5–4.5 h to complete the diaries over the entire IL phase. Accelerometers will be worn on a belt clip placed at the right hip (i.e., the right anterior iliac crest) and do not require any attention from participants. Participants are instructed to wear the accelerometer during waking hours for 2 weeks and to recharge the battery at least every 5 days. Throughout the study, participants are encouraged to carry out their usual daily activities. The device has no monitor and does not provide activity feedback. Within 2 weeks of the end of the intensive longitudinal phase (1–15 days), participants return their materials (i.e., study phone and accelerometer) and complete a 30-minute exit session to receive feedback on their back posture and mobility. Each participant will be compensated with a minimum of €40 for this study.

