#### Hypothesis tests for intensive-longitudinal phase

For the IL data with measurement days nested in participants, multilevel models with daily LTPA as outcome will be calculated. Hypothesis tests for the fixed effects will inform us on the daily links between LTPA and its within- and between-person predictors. To test mechanisms from the back health behavior model (Fig. 1), we will specify within-person mediation models and test the indirect effects.

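### Daily recovery experience is rated in the evening about that same evening, so its same-day link with LTPA cannot test the directional job-resource hypothesis

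*Protocol article*

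**What the plan says.** The section on determinants classes recovery experience on the work side: "Theory-based job resources will include" job control, recovery experience and organizational health climate. Table 2 lists the daily items under job demands and resources. Of the three named resources, only job control and recovery experience are measured daily.

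The recovery items are asked in the evening questionnaire only, and all four refer to the evening of that day. The challenge item reads "This evening I did things that challenged me", and the relaxation item asks whether the time was used to relax. The other two concern not thinking about work and deciding for oneself what to do. The prompt comes at 9 pm, and under study design and procedures "Participants can delay responding until 3 h after the time prompt", so an answer can come as late as midnight.

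The within-person research questions state the hypothesis with a direction: "On days when individuals experience higher levels of job demands and lower levels of job resources than usual", lower LTPA than usual is expected. The association is to be examined on the same day and from the previous day to the next. No resource is exempted from the same-day part. In the intensive-longitudinal phase, "multilevel models with daily LTPA as outcome will be calculated", and that outcome is accelerometer MVPA outside self-reported working hours.

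**The concern.** A predictor in a directional hypothesis should be recorded before the outcome, or at least should not describe it. Here the score is a look back at how leisure time was spent, entered as a work-side predictor of activity in leisure time. A person who trains hard after work has done something challenging that evening, and a person who stays on the sofa has used the evening to relax. The activity can generate the rating rather than follow from it.

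At stake is the reading of one construct in a stated within-person hypothesis. A positive same-day coefficient could be reported as job resources supporting activity, and a null or negative one as evidence against that. Either result could come from what the items ask. The Discussion presents the temporal alignment of predictors in the behaviour change process as something the study can test. For same-day recovery experience, the data do not provide that alignment.

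**Working it through.** **1. Timing and content, side by side**

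| Daily variable | Asked | Describes | Describes leisure within the LTPA window? |
|---|---|---|---|
| Time pressure | 3 pm | work that day | no |
| Job control | 3 pm | work that day | no |
| Recovery experience, 4 items | 9 pm, open to midnight | the evening of that day | yes |
| LTPA (outcome) | continuous, accelerometer | MVPA outside working hours | – |

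Recovery experience is the only named daily job demand or resource that rates leisure time. Activity before work also precedes the 3 pm ratings, but those items do not describe it. Splitting the accelerometer record at the time of the recovery rating would not help, because little of the day's leisure remains after 9 pm.

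**2. Which items overlap with activity**

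- Challenge item: sport in the evening can satisfy it directly, so it would rise with LTPA.
- Relaxation item: an inactive evening can satisfy it, so it may fall as LTPA rises.
- Detachment from work and self-determination items: neither describes activity.

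The items can therefore push in opposite directions.

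**3. How large could it be? (illustration only)**

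The documents give no figure for this, so there is none to reproduce. All values here are assumptions:

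- recovery has no true effect on LTPA;
- a share s of within-person LTPA variance falls in the evening, s = 0.4 or 0.8;
- the challenge item correlates a = 0.1 to 0.5 with evening LTPA, and the relaxation item b = 0, -0.2 or -0.3;
- the item parts unrelated to LTPA correlate 0.3 with each other;
- the four items are averaged.

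The spurious within-person correlation of the mean score with LTPA is r = √s × (a + b) / √V, where V is the variance of the sum of the four standardised items (4 plus twice the sum of the six pairwise correlations).

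Only the challenge item reflects activity (b = 0):

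- s = 0.4, a = 0.1: V = 7.59, r = 0.632 × 0.1 / 2.755 = 0.023
- s = 0.8, a = 0.5: V = 7.36, r = 0.894 × 0.5 / 2.713 = 0.165

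The relaxation item also falls with activity:

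- s = 0.8, a = 0.1, b = -0.3: V = 7.45, r = 0.894 × (-0.2) / 2.729 = -0.066
- s = 0.8, a = 0.5, b = -0.2: V = 7.12, r = 0.894 × 0.3 / 2.669 = 0.101
- a = -b (for example 0.2 and -0.2): r = 0

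A simulation of the same set-up gave 0.025, 0.165, -0.068, 0.103 and about 0. The challenge item taken alone gives √s × a, from 0.632 × 0.1 = 0.06 to 0.894 × 0.5 = 0.45.

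For scale, take the 150 persons and 14 days of the multilevel sample size section. The residual degrees of freedom are 150 × 13 - 1 = 1,949, and a two-sided 5% test rejects at |r| above 1.96 / √(1,949 + 1.96²) = 0.044. Much of the range above exceeds that threshold. This shows that a small artefact would matter, not that one is present.

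**The case against.** The strongest reply is that the article already plans the analysis that answers the concern, since job-resource links are examined from the previous day to the next as well as on the same day. It also calls these links associations, in a study that is observational throughout. The first part stands, and the fix relies on it. The second helps only in part: the hypothesis has a direction, and the same section refers to within-person predictors.

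A second reply is that the outcome is measured by accelerometer over all non-working time, including before work and on free days. That is correct. There is no shared self-report, and the overlap with the rated evening is partial. It remains an overlap of content and time, which an objective device does not remove.

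Three stronger readings are tempting, and the documents do not support them:

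- A reader might infer that the same-day association is guaranteed by the measure. Overlap is clear mainly for the challenge item, the relaxation item may pull the other way, and the two can cancel. The article does not say that the four daily items form one score.
- A reader might infer that the planned within-person mediation models are compromised. The article does not place recovery experience upstream of LTPA in any of them, and the model figure is not shown.
- A reader might take a high rejection rate from a simulation with an assumed reverse effect as evidence of contamination. Such a rate only restates the power to detect the correlation that was put in.

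**Conclusion.** The point holds in limited form. Item wording, time of asking, classification as a job resource and the same-day test are all stated in the article, so the point does not depend on detail left to an analysis plan. A same-day coefficient for recovery experience cannot separate a resource that enables activity from activity that produces the rating. This is clearest for the challenge item.

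Size and sign are unknown. The illustrative range of about -0.07 to +0.16 for a four-item mean rests on assumed evening shares, item correlations and scoring. The point concerns one construct in one within-person hypothesis. The previous-day analysis as planned, the 3 pm job variables, the recovery scale in the long-longitudinal questionnaires and the between-group comparison that sets the sample size are not called into question. It is an inexpensive improvement to the analysis, not a fault in the study as a whole.

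**What to change.** Change the analysis wording as follows:

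1. Base the directional test of recovery experience on the planned lagged analysis, with recovery on the evening of day t-1 predicting LTPA on day t, adjusted for LTPA on day t-1. The adjustment is needed because the previous evening's rating may itself reflect the previous evening's activity.
2. Report the same-day link between recovery experience and LTPA as descriptive and non-directional, showing the challenge and relaxation items separately.
3. Let job control carry the same-day job-resource hypothesis.

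No new data are needed and the items stay as they are. The main cost is that the same-day resource test then rests on a single item. The lagged analysis, which is planned anyway, has at most 13 day-pairs per person from 14 days.
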